#### Health and social service providers

3.5.4

Inclusion criteria are individuals who work at health and social services that support eligible older participants or volunteers in the target LGA, including the *Connect Local* program and the Community Connectors. Researchers will obtain information on health and service providers engaged in the program from the Community Connector and contact them directly to ask them to participate in the evaluation.

### Data collection

3.6

#### Procedures

3.6.1

Data will be collected either by researchers via the phone, in-person, in paper-based surveys, or by Community Connectors during program operations. Study data will be collected and managed using REDCap electronic data capture tools hosted on a secure server at Bolton Clarke (68), which only researchers will have access by password. Table 2 outlines the different levels and the data collected, while Table 3 outlines the time points of data collection. If data collection causes distress to participants, interviewing will be immediately halted and existing escalation procedures will be followed, including referral back to the referring healthcare provider (community members), service responsible (volunteers), or external mental health services.

**Table 3 tab3:** Schedule of enrolment, interventions and assessments, per SPIRIT guidelines (50).

	Study period				
Timepoint:	Screening	Baseline	3-months	6-months	12-months
Enrolment					
Screening	X				
Informed consent	X				
Intervention					
*Connect Local* intervention					
Usual care (no intervention)					
Assessments					
Single-item measure of loneliness (69)	X				
UCLA – LS 3 (58).	X	X	X	X	X
Lubben Social Network Scale (LSNS-6) (70).	X				
5 item Geriatric Depression Scale (GDS 5) (61).	X	X	X	X	X
Demographic information		X			
UCLA-LS4 (71).		X	X	X	X
Lubben Social Network Scale (LSNS-18) (59)		X	X	X	X
Mini-Social Phobia Inventory (Mini-SPIN) (60).		X	X	X	X
Warwick-Edinburgh Mental Wellbeing Scale (WEMWBS) (63);		X	X	X	X
EQ-5D-5L (62);		X	X	X	X
Goal attainment (64).		X	X	X	X
Community service impact survey				X	X
Resource use questionnaire		X	X	X	X
Perceptions (acceptability), use and satisfaction with program			X		
Process data			X	X	X
Perspectives of staff in General practice and other referral agencies			X	X	X

#### Outcomes: intervention

3.6.2

The aim of this evaluation is to assess the participant outcomes, and program effectiveness and impact from the Individual, Community and Health Service perspectives.

##### Individual level

3.6.2.1

This is the level at which individuals are impacted directly, including older community members, volunteers and health and social service providers.

For older community members, we will consider the primary outcome as a mean change in loneliness, from baseline at 3, 6 and 12 months for participants receiving the *Connect Local* program, when compared to the comparator group. This will be measured using UCLA-3 as informed by previous research that support the sample size calculations (58). At this stage, there is insufficient research data to calculate sample size when using UCLA-4 (57), however this tool has been recommended for use by community organisations by Australia’s national network, Ending Loneliness Together (71), therefore we will also utilise this tool to capture loneliness to ascertain whether it can be utilised with this cohort in future studies.

As outlined in Tables 2, 3, secondary outcomes, including social isolation, social anxiety, depressive symptoms, and improvement in quality of life and wellbeing, are a mean change from baseline at 3, 6 and 12 months for participants receiving the *Connect Local* program, when compared to the comparator. Achieved goals, as measured by the Goal Attainment scale (64), will also be gathered from the intervention group.

For community volunteers involved in the *Connect Local* program, as per Tables 2, 3, we will collect health-related quality of life and wellbeing measures at baseline, 3, 6 and 12 months.

Perceptions of the program will be collected from community members in the intervention group, volunteers and service providers involved in referred to the *Connect Local* program through interviews or focus groups at three months from participant baseline. Questions will invite participants to share their thoughts around the following aspects of the program: Relational (trust and trustworthiness, obligations and expectations, identity and identification), Cognitive (shared language, codes and narratives; shared values, attitudes and beliefs; and shared goals and purpose), and Structural (roles, rules, precedents and procedures).

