### Program effectiveness

3.1

Compared to the comparator group, older people receiving the intervention will, when compared to baseline, report at 3-, 6- and 12-months follow-up:

(i) a reduction in loneliness, social isolation and/or depressive symptoms;(ii) improvement in wellbeing and quality of life;(iii) increased access to activities/services in the community.

Three months after participation in the program, community volunteer participants will have improved wellbeing and quality of life when compared to baseline.

It is hypothesised that all stakeholders: intervention, volunteer and service provider participants will also have a positive perception of and experience with the program.

*Research question for older participant cohort using PICO:*

Does participation in the *Connect Local* social connection program reduce loneliness, social isolation and/or depressive symptoms, improve wellbeing and quality of life and increase access to activities/services in community of older Australians when compared to a similar group who do not have access to a similar program?

*Research question components for stakeholders using SPIDER:*

Sample: volunteers and service provider participants;

Phenomenon of interest: perception and experience of program;

Design: prospective surveys and semi-structured interviews;

Evaluation: impact on community and health services, and perceptions of the program;

Research type: mixed methods.

Question: What are the perceptions and experiences of volunteers/service provider participants after being a part of the *Connect Local* program?

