###### Sample size calculation

3.6.2.3.1

The primary outcome is a reduction in loneliness at 3 months for participants receiving the *Connect Local* program, when compared to the comparator group. A program conducting similar activities found a statistically significant reduction in mean UCLA-3 scores of 0.85, with a medium effect size of 0.37 (73). Using this effect size at 0.05 alpha, 76 participants are required in the intervention group to reach 0.9 power. Allowing for 15% attrition at the 3 month follow up, we have increased the sample size to 88. A matched comparator group will be recruited at a 1:1 ratio, as such a total of 176 participants will be recruited to the intervention and comparator groups.

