For quantitative, binary or dichotomous individual level outcomes (scales that have cut-off scores: loneliness (UCLA-3), social anxiety, depressive symptoms) additional analysis will be undertaken addressing the research question: do the interventions differ in their effectiveness, such that individuals in the intervention group experience a greater improvement in their probability of achieving the desired outcome compared to those receiving usual care. Generalised linear mixed models (GLMMs) for dichotomous outcomes will be used as well as GEE. The typology of missing data will be investigated to make sure that the assumptions of the adopted statistical technique are not violated. Our choice of GLMMs is based on the specific characteristics of the data, as well as the advantages provided by GLMMs in handling dependent responses in longitudinal or repeated measures studies. As highlighted in Breslow and Clayton (75), GLMMs incorporate random effects into the linear predictors and are particularly well-suited for modelling the dependence among response variables in such study designs.

Selection of the model that best fits the data will be based on the low goodness-of-fit measures such as the Akaike information criterion (AIC) and Bayesian information criterion (BIC). Additionally, the log-likelihood ratio test will be employed as another method for evaluating model fit.

All quantitative community and system level variables, as well as the goal attainment will be analysed descriptively. Descriptive statistics will be presented as proportions, means (standard deviations) or, for variables that did not conform to a normal or log-normal distribution, medians (interquartile range).

Statistical analysis will be performed using STATA V.15.0 (STATA Corp LP., College Station, Texas, United States). We will use a Type I error rate of 5% to indicate statistical significance, with 95% confidence intervals (CI).

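### The primary outcome is set at 3, 6 and 12 months in one section and at 3 months only in the sample size section, and no deciding visit, contrast or joint test is named.

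*Protocol article*

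**What the plan says.** All references are to the protocol article.

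- **Section 3.6.2.1 (Individual level)** defines the primary outcome over three visits: "we will consider the primary outcome as a mean change in loneliness, from baseline at 3, 6 and 12 months". The comparison is with the comparator group and the instrument is fixed: "This will be measured using UCLA-3 as informed by previous research that support the sample size calculations". The same section gives the other scales a lower rank: "secondary outcomes, including social isolation, social anxiety, depressive symptoms, and improvement in quality of life and wellbeing, are a mean change from baseline".
- **Section 3.6.2.3.1 (Sample size calculation)** defines it at one visit: "The primary outcome is a reduction in loneliness at 3 months for participants receiving the" programme, again against the comparator group. The effect size of 0.37, alpha of 0.05, power of 0.9, 76 participants and 15% attrition at the 3-month follow-up all follow from that sentence.
- **Section 3.1 (Program effectiveness)** hypothesises that intervention participants will "report at 3-, 6- and 12-months follow-up" several benefits relative to the comparator group. Item (i) is "a reduction in loneliness, social isolation and/or depressive symptoms".
- **Section 3.7.1.1 (Quantitative data analysis)** specifies linear mixed models with group, time and group-by-time terms, and states: "We will use a Type I error rate of 5% to indicate statistical significance". It does not say which coefficient, visit contrast or joint test answers the primary question.

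**The concern.** Two sections define the same item and give different answers. Section 3.6.2.1 points to the sample size work as the reason for choosing the UCLA-3, so the two are meant to describe one outcome. An analysis plan could not settle the matter without overriding one of the two statements.

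Two things are at stake. First, if the deciding visit is left open, primary success could be claimed at whichever of the three visits is significant, and the error rate would no longer be 5%. Secondly, the planned size belongs to one visit. If 6 or 12 months is read as primary, the 15% attrition allowance does not apply, because it is stated for the 3-month follow-up. The effect size has not been argued for the later visits either.

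The wording of 3.1(i) adds to the uncertainty. It places loneliness, social isolation and depressive symptoms side by side, whereas 3.6.2.1 makes only loneliness primary.

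**Working it through.** **1. The definitions side by side**

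| Section | Outcome | Visits |
|---|---|---|
| 3.6.2.1 | Change in UCLA-3, between groups | 3, 6 and 12 months |
| 3.6.2.3.1 | Reduction in loneliness (effect taken from UCLA-3), between groups | 3 months |
| 3.1(i) | Loneliness, isolation, depressive symptoms (and/or) | 3, 6 and 12 months |
| 3.7.1.1 | Each continuous outcome by mixed model | Deciding contrast not named |

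The first two rows cannot both be the definition of the primary outcome.

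**2. What the stated sample size covers**

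Inputs from 3.6.2.3.1: effect size 0.37, alpha 0.05, power 0.9. The sides of the test are not stated; two-sided is assumed. The one-sample (paired) normal formula gives

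n = ((1.960 + 1.2816) / 0.37)² = 76.75.

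This matches the stated 76 to within rounding. The stated 88 corresponds to 76 × 1.15 = 87.4, rounded up. So the figure is for one comparison at one visit, and the attrition is for that visit.

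The formula that reproduces 76 is a within-group one. For a between-group difference of 0.37 standard deviations, the simple two-sample formula gives 2 × 76.75 = 153.5, so 154 per arm. At 76 per arm the power is Φ(0.37 × √(76/2) − 1.960), about 0.63, with no gain assumed from baseline adjustment. This is a separate matter. It is noted because agreeing on 3 months would not by itself validate 76.

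**3. Error rate if any one of three visits may count as success**

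Assumptions: no true effect at any visit; three normal test statistics with a common correlation r; each compared with ±1.96. The documents give no correlations, so r is varied from 0.4 to 0.8. With u standard normal (density φ) and c = 1.96:

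- Any significant result: 1 − ∫ [Φ((c − √r·u)/√(1−r)) − Φ((−c − √r·u)/√(1−r))]³ φ(u) du
- Any significant result favouring the intervention: 1 − ∫ [Φ((c − √r·u)/√(1−r))]³ φ(u) du

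| Assumed r | Any direction (nominal 5%) | Favourable only (nominal 2.5%) |
|---|---|---|
| 0 (upper limit) | 1 − 0.95³ = 14.3% | 1 − 0.975³ = 7.3% |
| 0.4 | 13.1% | 6.6% |
| 0.8 | 9.8% | 4.9% |

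Since the hypothesis is a reduction in loneliness, the right-hand column is the rate of false claims of benefit. The middle column is the one to compare with the 5% in 3.7.1.1.

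**4. Readings with no inflation**

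If significance is required at all three visits, the chance of false success cannot exceed that of a single test. If one joint group-by-time test decides, there is one test at 5%. If 3 months alone is primary, there is again one test at 5%. The article does not say which reading applies.

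**The case against.** It can fairly be said that the mixed model in 3.7.1.1 need not imply separate tests at each visit, and that the visits are joined by *and*, which could mean all are required. The choice of contrast and the handling of multiplicity are also commonly left to an analysis plan, which is not at hand. Most of this stands. The error-rate figures are therefore conditional, and the absence of a multiplicity method is not itself the finding. What these arguments do not remove is the conflict between 3.6.2.1 and 3.6.2.3.1, which lies in the protocol text.

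A reader might infer something stronger: that 3.1(i), with three domains and three visits, allows success in nine ways, each tested at an unadjusted 5%. The documents do not support this. Section 3.6.2.1 already makes social isolation and depressive symptoms secondary, so at most three visits are in play for the primary outcome. The and/or phrase also describes the programme's aim and its target population (sections 1.1, 1.2 and 3.5.1), and is nowhere stated as a rule for declaring success. Separate testing of each domain and visit would have to be inferred from silence in 3.7.1.1. An error rate for nine tests is therefore not put forward here.

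It can also be said that 3 months is not the obvious choice, since section 1.3 and the Discussion stress medium- and longer-term outcomes. That is fair. The need is for one named visit, not necessarily that one.

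**Conclusion.** The contradiction is real and should be corrected before analysis: the primary outcome has two incompatible time definitions and no stated rule for deciding between them. The stated sample size and attrition allowance belong to the 3-month definition only.

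If any of the three visits may count, the false-positive rate is about 10% to 13% instead of 5%, or about 5% to 6.6% instead of 2.5% in the favourable direction. This rests on assumed correlations of 0.4 to 0.8 and on the any-visit reading. Under an all-visits rule or a single joint test there is no inflation.

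Hypothesis 3.1(i) is a lesser, related inconsistency: it is wider than the designated primary outcome, although the ranking in 3.6.2.1 is itself clear.

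**What to change.** 1. Name one primary time point for the between-group difference in change in UCLA-3 from baseline, and state it identically in 3.6.2.1 and 3.6.2.3.1. The 3-month visit is the one the sample size section already uses. If another visit is chosen, restate the sample size and the attrition allowance for it.
2. Make the remaining visits secondary.
3. Reword 3.1(i) so that loneliness is the confirmatory hypothesis and social isolation and depressive symptoms are secondary, as 3.6.2.1 already has them.

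The cost is a change of wording in three sections, plus a new calculation if the visit is not 3 months. The sponsor gives up the option of claiming primary success at another visit. The basis of the 76 needs its own check, since it reproduces only as a within-group calculation.

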##### Community level

3.6.2.2

As per Table 2 the following indicators will be collected to evaluate the impact of the program on the broader community: the number of participants who access community activities/services, the number and types of services offered to and used by participants in both the intervention and comparator groups at baseline, 3, 6 and 12 months using the Resource Use Questionnaire [adapted from Fletcher (65)].

We will also ask community service and/or activity providers about the impact of the program on their services six monthly, using the Community Service Impact Survey (72), and their perspectives of the program through interviews or focus groups at three months from when participants were engaged in their program.

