**Identify** what matters to the individual and screen for loneliness, social isolation and depressive symptoms: the Community Connector holds a rapport-building conversation, involving open-ended questions and using motivational interviewing techniques guided by the NHS document ‘What matters to me?’ (56). The question topics have previously been codesigned with Community Connectors and community members to ensure they are fit-for-purpose for the local population, and include: expectations of the program, personal history in the area, past activities of interest, and when they remember being happy – where they were, who they were with, and what they were doing;**Work together** on generating goals that address a social need/s, and a develop a **plan** to achieve these goals by linking the individual to activities and/or services being offered in the target geographic area. This is based on the discussion on “What matters to me?” and what existing available programs and activities are in the region, as well as the community member’s level of digital engagement and any transportation requirements. Usually three or four programs/activities are generated for pursuing;**Support** the individual to access these activities/services using local resources such as volunteer support including transport. This involves the Community Connector reaching out to program/activity providers agreed to in point 2, and organising to meet with the community member at the program/activity location. This serves as an introduction and, if possible, have the community member participate or at least view the program/activity, to ascertain whether this is something they are interested in engaging with. If the community member is interested, the Community Connector facilitates ongoing engagement in the program/activity, as needed. If the community member is not interested in this program/activity, they pursue an alternative program/activity discussed previously; and.**Review** follow up to ensure that the activities and/or services are addressing their needs. Should there be any issues, the Community Connector may either engage with the service/activity provider to address them or work with the individual to develop a new goal, plan and access new activity/service.

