#### Older community members: intervention group

3.5.1

The inclusion criteria include being aged 65 years or older; understand and speak English sufficiently to understand and be involved in the program; live in the target LGA; community dwelling (including those experiencing homelessness); have at least one chronic health condition; are at risk or experiencing loneliness, social isolation and/or depressive symptoms. Screening tools are summarised in Table 2, loneliness will be assessed using both the Single Item Measure and UCLA-3 as per recommended national indicators of loneliness (66).

**Table 2 tab2:** Intervention outcome evaluation methods.

Evaluation component *Definition*	Indicators	Methods and tools
Individual level *Impacting individuals directly*	*Older person participants:*	
	Loneliness	Single-item measure of loneliness: How often do you feel lonely?, responses: often or always, some of the time, occasionally, hardly ever or never (often or always, some of the time indicating loneliness)	UCLA-4 (57)
UCLA-3 (score of ≥6 indicates at risk of loneliness) (58)
Social isolation	Lubben-6 (score ≤ 12 indicates at risk for social isolation) and − 18 (59);
Social anxiety	Mini-SPIN (Social Phobia Inventory, SPIN) (60);
Depressive symptoms	GDS-5 (score of ≥2 is indicative of depression) (61);
Wellbeing and quality of life	Physical wellbeing (and QoL): EQ-5D-5L (62); Mental wellbeing: Warwick-Edinburgh Mental Wellbeing Scale (WEMWBS) (63);
Goals attained^+^	Goal Attainment (64)^+^.
Perceptions of program^+^	Interviews on perceptions of the program^+^.
*Service providers:*	
Perceptions of program	Interviews/focus groups on perceptions of the program.
*Volunteers:*	
Wellbeing and quality of life	Physical wellbeing (and QoL): EQ-5D-5L (62); Mental wellbeing: Warwick-Edinburgh Mental Wellbeing Scale (WEMWBS) (63);
Perceptions of program	Interviews/focus groups onperceptions of the program.
Community level *Impacting broader community*	*Older person participants:*	
	Access to activities/services Number and types of services offered to participants	Resource use questionnaire [adapted from Fletcher et al. (65)]
	*Community service providers:*	
	Impact of program on community services	Community service impact survey [adapted from NHS (56)]
	Community service provider Satisfaction with program	Interview/focus group with community service providers

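### Services offered are counted as an access outcome, but offers come from the Connector's own planning step, so a group difference in them shows delivery and is not evidence for hypothesis 3.1(iii)

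*Protocol article*

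**What the plan says.** Section 3.1 states the third effectiveness hypothesis for older participants as "increased access to activities/services in the community". It is set against the comparator group and relative to baseline, and participants are to "report at 3-, 6- and 12-months follow-up".

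Two places define how access is measured, and they differ:

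- Section 3.6.2.2 (Community level) lists "the number of participants who access community activities/services" and then "the number and types of services offered to and used by participants in both the intervention and comparator groups". Both are collected "at baseline, 3, 6 and 12 months using the Resource Use Questionnaire".
- Table 2, community-level row for older participants, reads "Access to activities/services Number and types of services offered to participants". Services used are not named there.

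Section 3.4 describes what the Connector does. In the planning step, "Usually three or four programs/activities are generated for pursuing". In the support step, the Connector contacts the providers, "organising to meet with the community member at the program/activity location", so that the person can join in or at least see what is on offer. If the person is interested, the Connector helps them to continue. If not, the pair moves to another activity on the list.

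Section 3.4.1 gives the comparator group its usual access to local activities without the program. Section 3.7.1.1 has all quantitative community-level variables analysed descriptively.

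**The concern.** An effectiveness indicator should be able to come out unfavourably even when the program is delivered exactly as planned. A count of services offered cannot readily do so. The Connector produces the offers as a programme step, and the comparator group has no one in that role. One quantity is then being used both as the dose and as the effect of that dose.

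A milder version of the problem affects services used. The support step includes accompanied introductory visits. The indicators as stated do not distinguish such a visit from attendance on the participant's own initiative.

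At stake is how 3.1(iii) will be read. If the reported table shows many more services offered in the intervention group, a reader may take this as improved community access, when it may show only that Connectors did their job. Because Table 2 names offers as the only quantity under access, this is a likely way for the result to be presented.

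**Working it through.** The article gives no figure for the access outcome, so there is nothing to reproduce. The check compares the indicators with the intervention's own content.

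**Step 1: which indicator belongs to the participant and which to the program?**

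| Indicator | Where stated | What produces it in the intervention group | Counterpart in the comparator group |
|---|---|---|---|
| Services offered | Table 2; section 3.6.2.2 | Connector's planning step (section 3.4), plus any usual offers | Usual offers only (section 3.4.1) |
| Services used | Section 3.6.2.2 only | Participant's own attendance, possibly plus accompanied introductions | Participant's own attendance |
| Number of participants who access | Section 3.6.2.2 | As for services used, counted once per person | As for services used |

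**Step 2: built-in difference in offers.** Let *u*₁ and *u*₀ be the mean number of offers from usual sources per person in the intervention and comparator groups. Let *k* be the number generated with the Connector, usually 3 to 4 by section 3.4. If those activities are recorded as offers:

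difference in offers = (*u*₁ + *k*) − *u*₀ = *k* + (*u*₁ − *u*₀)

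The article gives neither *u*₁ nor *u*₀, so values must be assumed:

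- If *u*₁ = *u*₀, at whatever level, the difference is 3 to 4.
- If comparator participants receive one more usual offer than intervention participants, it is 3 − 1 = 2 to 4 − 1 = 3.
- For the difference to vanish, comparator participants would need 3 to 4 more usual offers per person.

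The comparator group therefore need not have zero offers for the difference to be built in. It is enough that usual offers do not differ much between the groups. None of this involves any change in what participants do.

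**Step 3: services used.** Let *v* be the number of accompanied introductory visits per person that the questionnaire records as use. It lies between 0 (the questionnaire excludes them) and one per activity introduced (every visit counts). The article gives neither the recording rule nor the share of introductions that lead nowhere, so *v* has no derivable value. Its influence at 6 and 12 months depends further on the recall period and on how long Connector support lasts, and neither is stated.

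**Step 4: where offers belong.** Section 3.6.4.3 already assesses fidelity from administrative data on delivery of the four program components. Generating a plan of activities is one of those components, so offers have a natural place there.

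**The case against.** The best defence is that raising access is exactly what the program sets out to do, so some overlap between intervention and outcome is intended. That stands for access and use. It does not stand for offers, because an offer that is never taken up is not access.

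A reader might infer several stronger things that the documents do not support:

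- **That delivering the program automatically fulfils 3.1(iii).** No test, threshold or success rule is attached to access, and the analysis is descriptive. Section 3.6.2.2 also lists a count of persons who access activities, and someone who tries and rejects four activities adds no more to it than someone who settles into one.
- **That an accompanied visit counts as use.** No section says so. The adapted Resource Use Questionnaire is not shown and may already distinguish a single look from regular attendance. What can be said is that the stated indicators do not make the separation.
- **That comparator participants receive no offers.** They keep their usual access and are recruited through a hospital and a care provider, either of which may suggest services.
- **That the outcome should be lasting engagement.** The hypothesis says access. A minimum-attendance rule would replace the outcome with another one, and the article gives no basis for a particular cut-off.
- **That the Social Return on Investment ratio is biased.** Section 3.6.3.1 lists the outcomes to be monetised, and activity counts are not named among them. Box 1 compares service information between the groups to estimate displacement, but neither a bias nor its direction can be shown from that.

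Follow-up also helps. Use is collected in both groups at baseline, 3, 6 and 12 months, so the later visits can show whether it persists once Connector contact has tapered. Finally, the Table 2 entry may be two lines run together in extraction. Even then, services offered is the only count the table names for access, and use is absent.

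**Conclusion.** The concern holds in a limited form. Table 2 and section 3.6.2.2 define the access indicator differently, and both include services offered. A between-group difference in offers is largely built in: about three to four per participant if the planned activities are recorded as offers and usual offers are similar in the two groups. It reflects delivery and should not be read as support for 3.1(iii).

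Counts of services used may also partly reflect delivery while Connector support continues. That is a possibility left open by the stated indicators, and its size is unknown. The number of participants who access activities and the number of services used remain legitimate measures of the hypothesis.

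This is a non-primary outcome with a cheap remedy. It is worth correcting before results are tabulated, and it does not threaten the loneliness comparison.

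**What to change.** 1. Reconcile Table 2 with section 3.6.2.2 so that both state the same access indicators.
2. Move services offered to the fidelity measures in section 3.6.4.3 and stop presenting it as an effectiveness indicator.
3. Judge 3.1(iii) on the number of participants who access activities or services and on the services used, at 3, 6 and 12 months, with one definition applied in both groups.
4. Record Connector-accompanied introductory visits separately and show use with and without them, with emphasis on 6 and 12 months. Showing both matters because the exclusion can affect only the intervention group, while comparator visits accompanied by family or carers would still count.

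The cost is one or two extra items in a questionnaire that is already being adapted, and probably a smaller apparent increase in access. If data collection is too far advanced to add items, steps 1 to 3 still need only rewording. For step 4, the program's administrative records of component delivery may show which visits were accompanied.
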